**Fig. 2 Fig2:**
[figure not shown]
SPIRIT schedule of enrolment, intervention and assessments

#### Secondary outcomes

The secondary outcomes include baseline changes in anxiety and depression scores (GAD-7 and PHQ-9), disease-related parameters and the number of sessions attended by the follow-up. The follow-up interview will gather concrete data on the counsellor thereby enabling us to evaluate which form of psychological support (psychotherapy, counselling, psychiatric treatment or internet-based CBT) was used or to identify patients’ reasons for not using psychological health care.

Besides anthropometric data (age, gender, height, weight, body mass index and disease duration), the following disease-related parameters will be assessed: the need for technical aids (e.g. a wheelchair or oxygen), daily treatment duration, global assessments of limitations in daily life and pain, days absent from school or work, missed clinical visits and adherence measures using the Medication Adherence Rating Scale, German version (MARS-D) [28]. For diabetes (HbA1c), lung diseases (FEV1 expected) and juvenile idiopathic arthritis (Juvenile Arthritis Disease Activity Score) disease-specific parameters will be assessed. We will examine possible serious adverse events (SAEs) associated with the present screening and MI education approach. Gender-specific results will be analysed.

Audio-recorded MI/TAU conversations will also be quantitatively and qualitatively analysed using standardised tools (e.g. the motivational interviewing treatment integrity check) to assess treatment fidelity.

#### Screening measures

##### Generalised Anxiety Disorder Screener

GAD-7 is a practical self-report anxiety questionnaire. The occurrence of the seven core symptoms of generalised anxiety disorder (DSM-5) can be scored from 0 = ‘not at all’ to 3 = ‘nearly every day’ during the last 2 weeks. GAD-7 scores range from 0 to 21. Good internal consistency is reported with Cronbach’s α between .79 and .91 [29]. GAD-7 has been successfully used in adolescents [30, 31]. For the current study, a cut-off of ≥7 will qualify as a positive result [32–34]. A threshold of 15 points will indicate a red flag for severe anxiety symptoms [35].

##### Patient Health Questionnaire

In the PHQ-9 depression module, which is derived from the full Patient Health Questionnaire, nine DSM-5 criteria are scored from 0 = ‘not at all’ to 3 = ‘nearly every day’. Internal reliability estimates range from .86 to .89 using Cronbach’s α, and the 2-day test–retest reliability is estimated at .84 with nearly identical mean total scores [36]. For the current study, a cut-off of ≥7 will qualify for a recommendation of psychological treatment, as a score of >7 includes patients with major or minor depression [26, 37]. A cut-off of 20 points is the threshold for a red flag for major depressive symptoms [36].

#### Study design

##### Randomisation

Prior to enrolling the first participant, treating physicians in the specialised outpatient departments (Paediatric Allergy/Pulmonology, Diabetes/Endocrinology, Metabolic Diseases, Paediatric Cardiology, Gastroenterology, Rheumatology/Immunology and Paediatric Neurology) will be cluster-randomised to perform either MI or TAU. The dynamic allocation method of Pocock and Simon [38] will be used for randomisation and to estimate recruitment rates per physician (high or low) among the departments. The randomisation will be performed by an independent institute and blinded for the involved physicians [39]. MI-randomised physicians will sign a confidentiality agreement regarding MI to prevent potential trial-arm contamination.

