#### Training of the treating physicians in motivational interviewing

As a prerequisite, physicians randomised to the MI group will attend a 2-day MI training course certified by the Motivational Interviewing Network of Trainers. Their ability to practise MI will be evaluated based on recorded counselling sessions in a standard procedure known as the motivational interviewing treatment integrity check. The results will be delivered to and discussed with the physician to improve their MI skills. A 2-day course in MI has been shown to provide sufficient and successful training to clinicians [27].

Patients being treated by MI physicians who screen positive will be provided with two counselling sessions implementing MI. The first MI session will be conducted immediately after the screening and will last 15–50 min. Sessions will be audio-recorded after mutual agreement. A second appointment will be scheduled within 2–4 weeks for a second 30–50 min MI session. MI aims to engage the patient in discussing the option for professional psychological support, focusing on their thoughts when considering this option and discussing possible barriers as well as pros and cons. This technique will be used to consider change as an option and to change their behaviour, i.e. to meet with a psychotherapist or other health-care provider delivering psychological treatment or psychotherapy in our facility.

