##### Trial intervention and allocation

Patients will be recruited over 24 months. Eligible adolescents with chronic disease will be enrolled at the Düsseldorf University Children’s Hospital outpatient clinic. Patients and caregivers will be informed of the study prior to the clinical appointment.

The screening results will be displayed on the tablet computer to the treating physician with colour indicators (red flag: suicidality, major depression or severe anxiety, yellow: positive, green: negative), and the physician will discuss the result with the patient and their caregivers. Those with negative screening results will be briefly advised that psychological care is currently unnecessary for anxiety and depression, and a psychoeducational handout on coping with chronic conditions will be provided.

All participants with positive screening results (GAD or PHQ ≥ 7) will receive standardised written feedback with a recommendation to seek psychological counselling, They will be given contact addresses for local medical appointment schedulers. These participants will be allocated to either an MI or TAU intervention, depending on their treating physician’s randomisation. MI and TAU will be performed within the appointment framework. All patients will return for a second appointment within 2–4 weeks after inclusion (Fig. 2).

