### Data management and monitoring

#### Data analysis

The primary outcome will be confirmed by a logistic mixed model adjusting for the cluster structure in the data at a two-sided significance level of 5% [41]. Furthermore, the main outcome will undergo an exploratory analysis using logistic regression to adjust for covariates, such as age, sex and medical condition. The analyses will be performed in the intention-to-treat population.

Secondary measures will be analysed using non-parametric tests (number of psychological face-to-face or online sessions attended within the 6-month follow-up interval, missed clinical visits, acceptance to participate in the study and gender) and mixed ANOVAs (disease-related parameters and GAD-7, PHQ-9 and MARS-D scores).

Treatment safety will be analysed by comparing the SAE rates between groups by Fisher’s exact test.

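### Patients are recruited after the physician's arm is fixed and known at least to MI physicians, yet the confirmatory model omits baseline PHQ-9 and GAD-7 scores

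*Protocol article*

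**What the plan says.** **Timing of allocation.** The Randomisation section of the protocol article opens "Prior to enrolling the first participant, treating physicians in the specialised outpatient departments" and says these physicians are cluster-randomised to MI or TAU. It continues: "The randomisation will be performed by an independent institute and blinded for the involved physicians". The next sentence reads: "MI-randomised physicians will sign a confidentiality agreement regarding MI to prevent potential trial-arm contamination".

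**Knowledge of arm.** The section on training of the treating physicians states: "As a prerequisite, physicians randomised to the MI group will attend a 2-day MI training course". It also says: "The first MI session will be conducted immediately after the screening and will last 15–50 min".

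**Recruitment.** Under Trial intervention and allocation, patients are recruited over 24 months and receive MI or TAU "depending on their treating physician’s randomisation". The same section says: "Patients and caregivers will be informed of the study prior to the clinical appointment".

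**Safeguards.** Inclusion criteria plans to screen every eligible outpatient. Screening has patients complete GAD-7 and PHQ-9 on a tablet after consent and before they see the physician, with entry at a score of 7 or more on either. Primary outcome has blinded independent assessors.

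**Analysis.** Data analysis specifies for the primary outcome a "logistic mixed model adjusting for the cluster structure in the data", two-sided at 5%. Age, sex and medical condition are given as examples of covariates for an exploratory logistic regression. Baseline PHQ-9 and GAD-7 scores are not named there.

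**The concern.** When clusters are allocated first and patients enter later, randomisation of physicians does not by itself protect the comparison of patients. Whoever is invited, consents or is excluded can differ by arm if someone involved knows the arm. There is also a plausible reason for behaviour to differ: MI means a 15–50 minute session plus a second of 30–50 minutes, while TAU has no time requirement.

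Symptom severity plausibly predicts use of psychological care whatever the counselling style. If one arm enrols more severely affected adolescents, the primary comparison mixes the effect of MI with that difference. A random cluster effect accounts for correlation within physicians. It does not correct a systematic difference between arms in patient severity. The two measurements that would show and partly correct such a difference are collected from everyone at screening, but the confirmatory model does not use them.

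**Working it through.** **1. What follows from the text about who knows what, and when**

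| Step | Source in the protocol article | Consequence |
|---|---|---|
| Physicians randomised before first enrolment | Randomisation | Arm is fixed before recruitment |
| MI training is a prerequisite; first session follows directly after screening | Training of the treating physicians | An MI physician knows the arm before the first screen-positive patient |
| MI physicians sign an agreement about MI | Randomisation | Same conclusion; the date of signing is not given |
| Patient's arm follows the physician's | Trial intervention and allocation | No separate patient-level randomisation |
| Questionnaires come after consent and before the appointment | Screening | Scores cannot influence invitation or consent directly |
| Fixed cut-off of 7 | Screening | Screening status is not a matter of judgement |

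Untrained physicians can infer their arm, but the text does not say so. The routes left open are invitation, consent and exclusions that need judgement, such as acute suicidality or current substance abuse (Exclusion criteria).

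**2. The plan's own figures**

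Inputs from Sample size: 10% against 30%, two-sided 5%, power 80%, 10% for clustering, 15% drop-out.

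- Chi-square size: n = [1.96·√(2·0.20·0.80) + 0.842·√(0.10·0.90 + 0.30·0.70)]² / 0.20² = 61.6, rounded up to 62.
- Clustering: 62/0.90 = 68.9, rounded up to 69.
- Drop-out: 69/0.85 = 81.2, stated as 81; total 2 × 81 = 162.

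The stated sizes reproduce. Nothing in the sample size is wrong on this point.

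**3. Illustration of what a severity imbalance could do**

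These inputs are assumptions and do not come from the documents. Uptake is 8% in milder patients and 25% or 40% in more severe patients, the same in both arms (no MI effect). The severe share is 20% in TAU and 30% or 40% in MI.

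Arm rate = 0.08·(1 − h) + u·h, where h is the severe share and u the uptake in severe patients. Effective size per arm = 69/1.10 = 62.7. Rejection probability is from the normal approximation to the two-sided 5% two-proportion test.

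| u | h in MI | TAU rate | MI rate | Spurious difference (points) | Rejection probability |
|---|---|---|---|---|---|
| 25% | 30% | 11.4% | 13.1% | 1.7 | 0.060 |
| 25% | 40% | 11.4% | 14.8% | 3.4 | 0.087 |
| 40% | 30% | 14.4% | 17.6% | 3.2 | 0.078 |
| 40% | 40% | 14.4% | 20.8% | 6.4 | 0.155 |

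A second illustration fixes TAU at the planned 10% and takes 62 per arm. If selection alone moved the MI rate to 12%, 15%, 18% or 20%, the test would reject with probability 0.065, 0.134, 0.249 or 0.343. In the other direction, a true 30% seen as 25% or 20% would cut power from 0.80 to 0.60 or 0.34. These shifts are assumed as well.

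**The case against.** The strongest counter-case has five parts.

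**The blinding sentence.** A reader might infer that the plan falsely claims blinded physicians and so hides the risk. The documents do not support that. The word qualifies the randomisation carried out by an independent institute, and the next sentence openly speaks of physicians randomised to MI. Blinding during the trial is claimed only for outcome assessors. This objection stands. What remains is an ambiguity to be reworded.

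**The safeguards.** Screening all eligible outpatients, self-report before the physician is seen, and a numeric entry rule limit how far knowledge of the arm can shape the sample. This stands as narrowing the route. It does not settle who consents or who is excluded.

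**Silence about recruiting staff.** A reader might infer that staff who inform and consent patients know the arm. The article does not say either way, and a condensed article may leave this to the full protocol. It is no finding. Data analysis also already lists acceptance to participate among the measures to be analysed.

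**The covariates.** The model is not simply unadjusted: it accounts for clustering. The exploratory list is introduced as examples, so baseline scores are not ruled out there, and an analysis plan that is not shown may say more. This is fair, but the article does fix the confirmatory model, with no patient-level covariate named.

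**The magnitude.** Every driver is assumed. The illustration in step 3 implies TAU rates of 11.4% and 14.4% rather than the planned 10%, and the largest rejection rate comes from its most extreme corner. The spurious differences of 1.7 to 6.4 points compare with a planned effect of 20 points. All of this stands.

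**Conclusion.** The point holds in a limited form. Recruitment follows an allocation that at least the MI physicians know, so some recruitment bias is possible, though existing safeguards narrow it. The confirmatory model, as the article states it, does not use the baseline symptom scores that would correct the measured part of any severity imbalance. Using them is a cheap improvement worth making. The blinding wording is a secondary clarification.

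The size cannot be estimated from the documents. The rejection rate of about 6% to 16% rests on assumed uptake and severity shares, and the wider range of 6.5% to 34% on assumed shifts in uptake of 2 to 10 points. Neither range is evidence that this trial's type I error is inflated. Neither the sample size nor the blinding of outcome assessors is in question.

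**What to change.** 1. **Primary model (Data analysis).** Add baseline PHQ-9 and GAD-7 scores as prespecified covariates in the primary logistic mixed model. Keep the model without them as a sensitivity analysis.
2. **Wording (Randomisation).** State that allocation is concealed from physicians until assigned, that physicians are not blinded afterwards, and that outcome assessors are blinded.

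**Cost.** Both scores are already collected at screening, so no new data are needed. The odds ratio becomes conditional on these scores, which the report should say. Events are limited: at the planned rates, 0.10 × 69 + 0.30 × 69 = 27.6 are expected, and with no effect 2 × 0.10 × 69 = 13.8, so each score should enter as a single linear term. Adjustment reduces recruitment bias but does not remove it, because readiness to accept psychological care is not listed as a baseline measure. The rewording is an edit to one sentence.

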##### Trial intervention and allocation

Patients will be recruited over 24 months. Eligible adolescents with chronic disease will be enrolled at the Düsseldorf University Children’s Hospital outpatient clinic. Patients and caregivers will be informed of the study prior to the clinical appointment.

The screening results will be displayed on the tablet computer to the treating physician with colour indicators (red flag: suicidality, major depression or severe anxiety, yellow: positive, green: negative), and the physician will discuss the result with the patient and their caregivers. Those with negative screening results will be briefly advised that psychological care is currently unnecessary for anxiety and depression, and a psychoeducational handout on coping with chronic conditions will be provided.

All participants with positive screening results (GAD or PHQ ≥ 7) will receive standardised written feedback with a recommendation to seek psychological counselling, They will be given contact addresses for local medical appointment schedulers. These participants will be allocated to either an MI or TAU intervention, depending on their treating physician’s randomisation. MI and TAU will be performed within the appointment framework. All patients will return for a second appointment within 2–4 weeks after inclusion (Fig. 2).

##### Follow-up

Six months after study enrolment and their first MI or TAU session, the patients will be interviewed regarding their psychological counselling (see primary outcomes). Utilisation of psychological health care will be recorded in detail (number and type of sessions and missed appointments). Secondary outcomes will be assessed in the interview and by repeating the initial questionnaires (tablet, online or paper and pencil). Clinical data will be obtained from the most recent clinical visit.

#### Sample size

The proposed sample size for the baseline mental health screening assessment in our monocentric study is estimated at approximately *n* = 1,000 cases in 24 months. The prevalence of depression or anxiety symptoms is estimated at 15–20% in total across the disease spectrum [2] (Fig. 1).

The rate of successful mental health-care referrals for TAU is estimated at 10% [40] and we expect an increase to at least 30% for the intervention group. For a two-sided chi-square test with a power of 80% and a significance level of 5%, the software NQuery 8.0 (Statistical Solutions, 2018, Cork, Ireland) gives a sample size of *n* = 62 per group. We will correct the sample size by 10% for cluster effects, resulting in an estimated intra-cluster correlation coefficient of 2.5% and a sample size of *n* = 69 per group. To adjust for a 15% drop-out rate, the sample size per group is targeted at *n* = 81, treated by either MI physicians or TAU physicians, for a total of *n* = 162 patients (Fig. 1). All cases included in the study will be analysed by an intention-to-treat analysis.

### Data collection methods

Data on depression, anxiety (PHQ-9 and GAD-7), days absent from school or work, daily treatment duration, global assessments of limitations in daily life and pain, and adherence (MARS-D) will be collected directly from the patients (patient-reported outcomes) by a tablet questionnaire. Pseudonymised results will be stored on a secure local and national server. Physicians responsible for treating the participants medically will contribute additional medical information on case report forms at baseline and at the 6-month follow-up.

### Data management and monitoring

#### Data analysis

The primary outcome will be confirmed by a logistic mixed model adjusting for the cluster structure in the data at a two-sided significance level of 5% [41]. Furthermore, the main outcome will undergo an exploratory analysis using logistic regression to adjust for covariates, such as age, sex and medical condition. The analyses will be performed in the intention-to-treat population.

Secondary measures will be analysed using non-parametric tests (number of psychological face-to-face or online sessions attended within the 6-month follow-up interval, missed clinical visits, acceptance to participate in the study and gender) and mixed ANOVAs (disease-related parameters and GAD-7, PHQ-9 and MARS-D scores).

Treatment safety will be analysed by comparing the SAE rates between groups by Fisher’s exact test.

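### As named, the covariate-adjusted analysis of the main outcome and the non-parametric secondary tests ignore the physician clusters that were randomised

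*Protocol article*

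**What the plan says.** Under Randomisation, the protocol article says that treating physicians in the specialised outpatient departments "will be cluster-randomised to perform either MI or TAU". Under Trial intervention and allocation, patients follow their physician: "These participants will be allocated to either an MI or TAU intervention, depending on their treating physician". The Sample size section enlarges the groups by 10% for clustering and links this to an ICC of 2.5%.

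The Data analysis section names these methods:

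- **Primary outcome, confirmatory:** a logistic mixed model that accounts for clusters, two-sided 5%.
- **Primary outcome, adjusted:** "the main outcome will undergo an exploratory analysis using logistic regression to adjust for covariates, such as age, sex and medical condition".
- **Session counts and missed clinic visits, among others:** "Secondary measures will be analysed using non-parametric tests".
- **Symptom scores, adherence score and disease-related parameters:** mixed ANOVAs, without saying which factor is random or repeated.
- **Serious adverse events (SAEs):** "Treatment safety will be analysed by comparing the SAE rates between groups", by Fisher's exact test.

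Clustering is mentioned only for the first of these. No general sentence extends it to the others.

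**The concern.** When physicians are randomised, patients of one physician share that physician's habits, department and case mix. A between-arm comparison that counts each patient as independent understates the standard error. Ordinary logistic regression and standard rank tests do exactly that, while the sample size calculation of the same article takes the correlation to be non-zero.

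At stake are the service-use comparisons and the adjusted odds ratio for the main outcome. Their p-values would be somewhat too small, and the interval for the adjusted odds ratio somewhat too narrow. The adjusted and primary odds ratios would also differ in two respects at once, the covariates and the physician term, so a gap between them would be harder to interpret.

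**Working it through.** **Inputs from the Sample size section.** Rates 10% (TAU) and 30% (MI), two-sided 5%, power 80%, 10% cluster correction, ICC 0.025, 15% drop-out. Neither the number of physicians nor an ICC for any secondary outcome is given.

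**1. The plan's own figure.** With a mean rate of 0.20:

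n = [1.96·√(2·0.20·0.80) + 0.8416·√(0.10·0.90 + 0.30·0.70)]² / 0.20² = (1.1087 + 0.4610)² / 0.04 = 61.6, so 62 per group.

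Cluster step: 62 × 1.10 = 68.2, or 62 / 0.90 = 68.9; both round up to 69. Drop-out: 69 / 0.85 = 81.2, against 81 in the plan. The chain reproduces.

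**2. Implied cluster size.** The design effect is DE = 1 + (m − 1)·ICC. Setting DE = 1.10 and ICC = 0.025 gives m = 1 + 0.10/0.025 = 5 patients per physician.

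**3. Actual level when clusters are ignored.** The true standard error is √DE times the naive one, so a nominal 5% test has level 2·[1 − Φ(1.96/√DE)]. At DE = 1.10, √DE = 1.049 and 1.96/1.049 = 1.869. The level is 6.2%, coverage of a nominal 95% interval is 93.8%, and the interval is about 5% too narrow (1/1.049 = 0.953).

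**4. Sensitivity.** All rows after the first rest on assumed inputs.

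| Patients per physician | ICC | DE | Actual level |
|---|---|---|---|
| 5 | 0.025 | 1.10 | 6.2% |
| 10 | 0.025 | 1.225 | 7.7% |
| 10 | 0.05 | 1.45 | 10.4% |
| 15 | 0.05 | 1.70 | 13.3% |

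Unequal clusters add to this. With mean size 7, an assumed coefficient of variation of 0.65 and ICC 0.025, DE = 1 + [(1 + 0.65²)·7 − 1]·0.025 = 1.224, a level of about 7.6%. Simulation of that setting gave about 7.5 to 8%.

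**5. Rank test by simulation** (70 patients per arm, equal clusters, physician ignored). The Mann-Whitney level was 6.3% at 5 per physician and ICC 0.025, 7.2% at 10 and 0.025, and 9.6% at 10 and 0.05. With ICC zero it was about 4.5%. The formula in step 3 therefore serves for the rank tests too.

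**6. Fisher's test by simulation** (70 per arm, 5 per physician).

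| SAE rate (assumed) | Level, no clustering | Level, ICC 0.025 |
|---|---|---|
| 2% | 0.2% | 0.3% |
| 5% | 1.4% | 1.8% |
| 10% | 2.5% | 3.3% |
| 20% | 3.3% | 4.1% |

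Clustering raises the level, but from a conservative start. It passes 5% only with larger clusters, a higher ICC or frequent events, for example 6.1% at 10 per physician, ICC 0.05 and an SAE rate of 10%.

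**The case against.** The strongest reply is that this is a condensed article and the analysis plan, which is not shown, may specify the model terms. That disposes of much of the case on the mixed ANOVAs. The term usually means group by time within patient, but the text does not exclude a physician effect, so their omission of it is an inference. It does not dispose of the rank tests and the logistic regression. The article names those methods, directly after a model that is said to handle clusters, and in standard form they assume independent patients. An analysis plan could correct this only by modifying what is named.

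Several further points stand:

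- The confirmatory test is protected, and the adjusted analysis is labelled exploratory.
- Adjusting for medical condition may absorb part of the between-physician variation, because physicians work in disease-specific departments. The calculations above include no such covariate.
- The list given for the non-parametric tests also contains study acceptance and gender, which are not clearly between-arm comparisons. No intervals are specified for the rank or Fisher tests, so the coverage figure concerns the adjusted odds ratio.

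A reader might infer that every p-value other than the primary one is too small, safety included. The documents do not support that: Fisher's test stays below 5% at the plan's ICC with about 5 patients per physician. A reader might also expect levels of 15 to 25%. In simulation, such levels arise only at assumed ICCs of 0.10 to 0.20, four to eight times the plan's value, and the document gives no basis for those. Nor are the primary and adjusted odds ratios beyond comparison: at DE 1.10 the standard errors differ by about 5%.

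**Conclusion.** The point holds for the exploratory covariate-adjusted logistic regression and for the non-parametric between-arm tests of sessions attended and missed visits. Under the plan's own assumptions the error is modest: about 6.2% instead of 5%, and 93.8% coverage instead of 95%. It could be larger. The Randomisation section separates physicians with high and low recruitment, so unequal clusters are likely, and the ICC of 2.5% is given only for the primary outcome. How much larger cannot be read from the article.

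For the mixed ANOVAs this is a request to state the physician effect. For SAEs the independence assumption is wrong in principle but of little practical effect. The calculations assume a normal approximation and no gain from balancing departments in the allocation, which could offset part of the inflation. Severity is moderate.

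**What to change.** State that all between-arm comparisons account for the physician, and name the method for each:

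- **Adjusted main outcome:** the same logistic mixed model as the primary analysis, with age, sex and medical condition added.
- **Scores and continuous disease parameters:** linear mixed models with a physician random intercept, in addition to any repeated-measures structure within patient.
- **Sessions attended and missed visits:** a cluster-aware method, for example a rank test whose reference distribution comes from permuting physicians between arms, or a mixed model for counts.
- **SAEs:** counts per arm, with any p-value either labelled descriptive or obtained by a cluster-aware method.

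If the analysis plan already does this, a clarifying sentence is enough. Otherwise the cost is analysis-plan wording, a little programming and slightly wider intervals (about 5% at the plan's design effect). No new data and no design change are needed. It should be settled before results by arm are seen.

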### Study interventions

#### Screening

Anxiety and depression will be screened as part of the clinical routine. After providing informed consent, participants will complete the following screening questionnaires on a tablet computer in the outpatient clinic immediately prior to their scheduled appointment: the Generalised Anxiety Disorder 7-item scale (GAD-7) [23] and the depression portion of the Patient Health Questionnaire (PHQ-9) [24–26]. Patient-reported outcomes on disease-related parameters will be assessed after the standardised screening questionnaires (see below).

Immediate feedback will be provided based on the results of these screening tools. Positive screening, defined as either a GAD-7 or PHQ-9 score ≥ 7, will trigger a recommendation for supportive counselling (see Section 1.2). Negative screening results will be conveyed to the adolescent and a psychoeducational handout will be provided.

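### Mixed ANOVA on two time points tests change from baseline; adjusting for the baseline already collected would be more precise for the continuous secondary outcomes

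*Protocol article*

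**What the plan says.** All places are in the protocol article.

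- **Method.** Data analysis assigns the scores and disease parameters to "mixed ANOVAs (disease-related parameters and GAD-7, PHQ-9 and MARS-D scores". No baseline covariate is named for them. Covariate adjustment is mentioned only for an exploratory analysis of the primary outcome.
- **Outcome.** Secondary outcomes: "The secondary outcomes include baseline changes in anxiety and depression scores (GAD-7 and PHQ-9".
- **Time points.** Follow-up, six months after enrolment: "Secondary outcomes will be assessed in the interview and by repeating the initial questionnaires". For clinical data, Data collection methods has physicians supply "additional medical information on case report forms at baseline and at the 6-month follow-up". Each measure therefore has two values per patient.
- **Entry.** Screening: "Positive screening, defined as either a GAD-7 or PHQ-9 score ≥ 7". The score that admits a patient to the comparison is also that patient's baseline value.
- **Expected share screening positive.** Sample size: "The prevalence of depression or anxiety symptoms is estimated at 15–20% in total across the disease spectrum".

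**The concern.** With one baseline and one follow-up value, the term of interest in a mixed ANOVA is group by time, and that term compares mean change between arms. A change score fixes the slope of follow-up on baseline at 1. Questionnaire scores repeated after six months usually have a slope below 1, and two consequences follow.

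First, baseline noise is subtracted into the outcome and the standard error grows. Second, if one arm happens to start higher, it also appears to fall further, whatever the treatment does. For GAD-7 and PHQ-9, entry on a high score makes regression to the mean visible in both arms.

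The secondary comparisons are at stake, and no power was planned for them. Patients' baseline information would be partly wasted, and a chance imbalance would partly be read as effect.

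**Working it through.** **The plan's own figure.** The only sample size concerns the primary outcome: "For a two-sided chi-square test with a power of 80% and a significance level of 5"%, with 10% expected under TAU and 30% under MI. The usual formula gives [1.96·√(2·0.2·0.8) + 0.842·√(0.1·0.9 + 0.3·0.7)]² / 0.2² = 61.6, so 62 per group. Then 62 × 1.10 = 68.2, so 69, and 69/0.85 = 81.2, stated as 81, or 162 in total. This reproduces. The article gives no corresponding figure for the secondary scores.

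**Step 1: which test is planned.** In simulated data with 69 patients per arm and two time points, the group-by-time F was 8.546 and the squared t on change was 8.546. The two are identical. Testing the group main effect instead would be no better, because it averages in the pre-treatment score.

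**Step 2: measures not used for selection (MARS-D, continuous disease parameters).** Assume equal SD s at both times and correlation r.

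- Change score: variance 2s²(1 − r).
- Baseline-adjusted: variance s²(1 − r²).
- Ratio, adjusted to change: (1 + r)/2. Extra patients needed by the change score: 2/(1 + r) − 1.

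| assumed r | ratio | extra patients |
|---|---|---|
| 0.3 | 0.65 | 54% |
| 0.5 | 0.75 | 33% |
| 0.7 | 0.85 | 18% |

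**Step 3: GAD-7 and PHQ-9, after selection.** Selection narrows the baseline. In units of the unselected SD, let v be the baseline variance among those admitted. The follow-up is assumed to depend linearly on the patient's own baseline with slope r.

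- Baseline-adjusted: 1 − r².
- Change score: (1 − r²) + (1 − r)²·v.

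Simulating two normal scales and admitting the top 15–20% on either one gives v of about 0.70 at an inter-scale correlation of 0.5 and 0.46 at 0.7.

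| inter-scale correlation | v | r = 0.5 | r = 0.7 |
|---|---|---|---|
| 0.5 | 0.70 | 0.750/0.925 = 0.81 (23% more) | 0.510/0.573 = 0.89 (12% more) |
| 0.7 | 0.46 | 0.750/0.865 = 0.87 (15% more) | 0.510/0.551 = 0.93 (8% more) |

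At an assumed r of 0.3 the cost rises to about 25–38%: 0.910/1.135 = 0.80 for v = 0.46, and 0.910/1.253 = 0.73 for v = 0.70.

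**Step 4: imbalance.** If the arms differ at baseline by d, the change-score effect moves by −(1 − slope)·d. With slope 0.5, a difference of 1 point moves it by 0.5 points. With 69 per arm, the standard error of the baseline difference is √(2/69) = 0.17 baseline SD, or √(2 × 1.10/69) = 0.18 with the plan's cluster inflation. A difference of 0.2 SD is therefore ordinary. It shifts the effect by 0.14, 0.10 or 0.06 SD for slopes of 0.3, 0.5 or 0.7.

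**The case against.** **The planned test is valid.** Randomisation makes the change-score comparison unbiased on average, and regression to the mean affects both arms and cancels in expectation. This stands. A reader might infer that selecting on a high score biases the comparison. It does not, because the shift is conditional on the imbalance that happens to occur.

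**Few physicians.** A reader might also infer that few physicians were randomised, so that imbalance is likely. The article does not state their number. Its figures give 1 + (m − 1) × 0.025 = 1.10, so m = 5 patients per physician and 69/5, or about 14, physicians per arm. Dynamic allocation by the method of Pocock and Simon is also planned. The point does not rest on few clusters.

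**Selection is narrower than it looks.** Only GAD-7 and PHQ-9 are selected on, and only one of them needs to reach 7. MARS-D and the disease parameters are not selected on.

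**Adjustment is no guarantee.** It removes the imbalance shift when the imbalance is due to chance and one slope applies throughout. Lasting case-mix differences between physicians in different departments need not follow the patient-level slope.

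**Missing follow-up.** A model of the 6-month value also omits patients without that value, so drop-out is no argument for it over the ANOVA.

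**Detail may sit elsewhere.** Model terms commonly belong in an analysis plan that is not shown. However, the article does name the method and describes the score outcome as change. The point concerns that choice and not an omission.

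**Conclusion.** The point holds as a precision improvement for the continuous secondary outcomes. The planned test is valid but less efficient than baseline adjustment on the same data, and it carries (1 − slope) of a chance imbalance into the estimate.

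For GAD-7 and PHQ-9 the change score costs about 8–23% in patients at assumed correlations of 0.5–0.7. For measures not selected on, it costs 33% at an assumed r of 0.5. The size rests on assumed correlations, normal scales and equal variances before selection. All ratios are at patient level and ignore clustering. The documents do not support calling the secondary results biased or the trial's main conclusion affected: the primary logistic mixed model and N = 162 are untouched.

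**What to change.** For the continuous measures, replace the mixed ANOVAs with a linear mixed model of the 6-month value. Include arm, the baseline value of the same measure and a physician random intercept, so that clustering is handled as in the primary analysis. If patients with only one measurement are to be kept, use the constrained-baseline longitudinal version, in which both values are outcomes and the arms share a baseline mean. State that the adjustment addresses chance imbalance under a common slope.

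The cost is wording in the analysis section. Baseline and 6-month values are already collected, and neither sample size nor visits change. Fix the model before outcome data are seen by arm, so that the choice cannot depend on which arm started higher. If the full analysis plan already adjusts for baseline, only the article's wording needs to be aligned with it.
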